#### Physical measurements

Physical measurements are performed to calculate the cardiovascular risk score and to describe the patients' characteristics.

1. Anthropometric measurements. Body weight and height are measured for the calculation of the Body Mass Index (weight divided by height squared). Waist circumference is measured at the level midway between the lowest rib margin and the iliac crest.

2. Systolic and diastolic blood pressure is measured after 5 minutes of rest in seated position by Collin Press Mate (BP-8800, Komaki-City).

3. Blood samples are taken in order to determine:

• fasting plasma glucose: measured in plasma by means of a hexokinase-method (Roche Diagnostics GmbH, Mannheim, Germany).

• HbA_1c_: measured by High Performance Liquid Chromatography

• Total cholesterol, HDL-cholesterol and triglycerides by means of enzymatic techniques (Boehringer-Mannheim, Mannheim, Germany).

4. In addition, data are collected from the patients on:

• hospital admission days per 6 months

• number of visits to general practitioner per 6 months

• medication changes per 6 months

### Analyses

Comparability between the two groups will be assessed at baseline. On the basis of an intention-to-treat analysis, differences in changes between the intervention and the control group are measured with 95% confidence intervals at 12 months for both primary and secondary outcomes. For dichotomous outcome variables a multilevel logistic regression analysis will be used. To calculate differences between continuous variables a multilevel analysis will be used, to adjust for the clustering of observations of patients receiving care from the same GP, and for repeated measurements within one patient. We will also perform a per-protocol analysis with patients that have attended at least three CBT sessions.

We will adjust data for possible confounders: age, gender, weight at start of study, diabetes duration, level of education, depression, smoking, number of attended sessions, general practitioner, and type of health care provider (diabetes nurse or dietician).

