### Outcome assessment

Outcome measurements are assessed at baseline, and again after 6 and 12 months by means of self-reported questionnaires and physical examinations at the DCS. Physical examinations are performed by medical assistants of the DCS. These included weight, height, waist circumference, blood pressure, fasting blood glucose, HbA1c, triglycerides (at baseline and 12 months only), total cholesterol (at baseline and 12 months only) and HDL-cholesterol (at baseline and 12 months only). Demographic variables on age, gender, diabetes duration, marital status, ethnicity, level of education and eventual occupation are assessed at baseline by using a self-administered questionnaire, which also includes all secondary outcomes. The medical assistants ask the patients information on medication (the patient brings the packages of medication to the visit), hospital admission days and number of general practitioner visits. Patients are informed of their measurements by the diabetes nurse and dietician. Measurements are also send to their GPs.

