#### Primary outcome measures

The primary outcome measure is the difference between intervention and control group in change in cardiovascular risk score after 12 months. The cardiovascular risk score is based on the Oxford Risk Engine (algorithm that includes: age at diagnosis, duration of diabetes, sex, ethnicity, smoking status, systolic blood pressure, HbA_1c_, total cholesterol, HDL-cholesterol) [38].

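### The model for change in cardiovascular risk score does not include the baseline risk score, which costs precision and leaves the estimate sensitive to chance baseline imbalance

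*Protocol article*

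**What the plan says.** The Primary outcome measures section defines the endpoint: "The primary outcome measure is the difference between intervention and control group in change in cardiovascular risk score after 12 months". The Analyses section carries this through to every outcome, primary and secondary alike: "differences in changes between the intervention and the control group are measured with 95% confidence intervals at 12 months". Continuous outcomes are analysed with a multilevel model, "to adjust for the clustering of observations of patients receiving care from the same GP, and for repeated measurements within one patient".

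The same section lists ten adjustment variables, beginning "age, gender, weight at start of study, diabetes duration, level of education, depression, smoking, number of attended sessions" and ending with general practitioner and type of care provider. Baseline weight is named. The baseline value of the risk score is not, and neither are baseline systolic pressure, HbA1c or cholesterol.

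The score is computed from "age at diagnosis, duration of diabetes, sex, ethnicity, smoking status, systolic blood pressure, HbA_1c_, total cholesterol, HDL-cholesterol". The Outcome assessment section schedules "total cholesterol (at baseline and 12 months only) and HDL-cholesterol (at baseline and 12 months only", so the score can be calculated at two times only.

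The article does not say whether the baseline score enters the model as an outcome or as a covariate. If it is an outcome, the article does not say whether its mean is held equal across arms.

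**The concern.** A difference in changes with no baseline term fixes the slope of the 12-month score on the baseline score at 1. When the true correlation is below 1, this over-corrects for baseline. Two things follow:

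- The confidence interval is wider than it needs to be.
- The estimate is negatively correlated with the chance baseline difference. An arm that happens to start higher will appear to improve more.

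The baseline score has to be computed for each patient anyway to form the change, so this precision is given up for no saving. Because the same sentence governs the secondary outcomes, the point also reaches the continuous questionnaire scales measured at baseline. At stake are the width of the interval and the reading of the result if the arms differ at baseline. The validity of the test is not at stake.

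**Working it through.** **Inputs.** From the Sample size section: target difference in changes d = 5 points of absolute risk; SD = 10 points, described as the SD of the absolute risk but used for changes; two-sided alpha 0.05; power 90%; within-practice correlation r = 0.20, applied as a factor 1 − r; dropout 30%. The baseline-to-12-month correlation rho is not given, so a range is shown.

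**The plan's own figure.** 2 × (1.96 + 1.282)² × 0.10² × 0.8 / 0.05² = 67.3, rounded up to 68 per group. 68/0.7 = 97.1, which the article gives as 97. Both figures reproduce.

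**Variance.** Take equal SD s at both times.

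- Change score: 2s²(1 − rho).
- Baseline-adjusted: s²(1 − rho²).
- Ratio of adjusted to change score: (1 − rho)(1 + rho) / [2(1 − rho)] = (1 + rho)/2.

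If 10 points is the SD of both the level and the change, then 2(1 − rho) = 1 and rho = 0.5. This is the value that the plan's use of the figure implies.

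**Imbalance.** If the baseline difference between arms is D, the change-score estimate moves by −(1 − rho)D. The adjusted estimate does not move.

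**Results.** No allowance is made for the listed covariates. The power column takes 10 points as the SD of change, keeps the factor 0.8 and uses 68 per group.

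| rho | Variance reduction | CI narrower by | n per group for 90% power (plan: 68) | Power at 68 per group (change score: 90.3%) | Shift from a 2-point imbalance |
|---|---|---|---|---|---|
| 0.5 | 25% | 13.4% | 51 | 96.4% | 1.0 point |
| 0.8 | 10% | 5.1% | 61 | 93.0% | 0.4 point |
| 0.9 | 5% | 2.5% | 64 | 91.7% | 0.2 point |

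Without the factor 0.8, the change at rho 0.5 is from 83% to 92% power.

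The scaling matters for power. If 10 points is instead the SD of the level, the SD of change at rho 0.8 is 10 × √0.4 = 6.3 points. Power at 68 per group is then already 99.9% without adjustment.

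**How likely is a 2-point imbalance?** With a level SD of 10 points and 68 per group, the SE of the baseline difference is 10 × √(2/68) = 1.7 points, ignoring the stratification by practice. Two points is about 1.2 SE, which arises by chance in roughly a quarter of trials.

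**Simulation** (68 per arm, level SD 10 points, no effect, 20,000 runs):

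| rho | SE, change score (points) | SE, adjusted (points) | Correlation of change-score estimate with baseline difference |
|---|---|---|---|
| 0.5 | 1.72 | 1.50 | −0.50 |
| 0.8 | 1.09 | 1.04 | −0.32 |
| 0.9 | 0.77 | 0.75 | −0.23 |

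The adjusted estimate's correlation with the baseline difference was about zero. Both estimators averaged zero.

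**Does the repeated-measures wording already solve this?** With complete data at two times and a free baseline mean in each arm, the arm-by-time contrast equals the difference in mean changes. It comes close to baseline adjustment only if the arms share one baseline mean, which the article does not state.

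**The case against.** The strongest reply is that a difference in changes names the quantity to be estimated, not the model. A baseline-adjusted model estimates the same quantity, and so does a repeated-measures model with a common baseline mean. An article may leave the choice to the full protocol or analysis plan. It is true that the text does not exclude either model. But the article does list its covariates, in enough detail to name baseline weight, and leaves out the baseline value of its own primary outcome. The point is therefore about a stated choice that can be improved, not about missing detail.

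Four stronger readings are tempting and are not supported:

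- **Changes are compared with no adjustment at all.** They are not. The model is multilevel with ten covariates, and age, gender, diabetes duration and smoking overlap inputs of the score, so part of a baseline difference would be absorbed. The effect of this on the gain can go either way, because the ratio becomes (1 + rho_c)/2, with rho_c the correlation given the covariates. As an assumed illustration, let the covariates explain half the variance identically at both times and let rho be 0.8. Then rho_c = (0.8 − 0.5)/(1 − 0.5) = 0.6 and the reduction is 20% instead of 10%.
- **Selection on high HbA1c, BMI or smoking biases the comparison through regression to the mean.** Eligibility rests on the previous annual visit, newly diagnosed patients enter without these thresholds, BMI is not an input to the score, and patients are randomised within practices. Any regression acts equally on both arms in expectation.
- **A baseline imbalance passes in full into the effect.** Only a fraction 1 − rho does.
- **The trial is underpowered because of this.** The sample size was set for a difference in changes and takes no credit for baseline adjustment, so adjustment can only help.

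It also stands that rho may be high. Several inputs to the score are fixed or advance equally in everyone, and in that case the gain is a few percent.

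**Conclusion.** The point holds as one of efficiency and of robustness to chance imbalance. As written, the analysis has a larger variance than a baseline-adjusted one: the adjusted variance is (1 + rho)/2 of it, or 25%, 10% or 5% lower at rho 0.5, 0.8 or 0.9. The estimate also keeps a dependence on the baseline difference worth 1.0, 0.4 or 0.2 points per 2 points of imbalance.

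These figures assume equal variances at the two times and make no allowance for the listed covariates. Rho is not in the documents, and 0.5 is only what the sample-size calculation implies if its SD applies to both levels and changes. The effect is modest if rho is high, but the improvement is specific and free. Settling it in advance also avoids a choice between two estimates after an imbalance has been seen. The Analyses section compares the arms at baseline but does not say what follows if the risk score itself differs.

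**What to change.** In the Analyses section, state that the 12-month risk score (or its change, which gives the same arm coefficient) is modelled on treatment arm with the baseline risk score as a covariate and practice in the multilevel model. A repeated-measures model with one common baseline mean for both arms is an equivalent alternative in practice, and should be named if that is the intention. Use the same form for each continuous secondary outcome measured at baseline. The patient-satisfaction questionnaire has no baseline assessment, so it falls outside this.

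The cost is one sentence. No new measurement is needed, the sample size need not change, and the quantity estimated remains the between-group difference in change. The sentence should be fixed before outcomes are compared by arm.

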**Methods:**

Patients with type 2 diabetes will be selected from general practices (n = 13), who are participating in a managed diabetes care system. Patients will be randomised into an intervention group receiving cognitive behaviour therapy (CBT) in addition to managed care, and a control group that will receive managed care only. The CBT consists of three to six individual sessions of 30 minutes to increase the patient's motivation, by using principles of MI, and ability to change their lifestyle, by using PST. The first session will start with a risk assessment of diabetes complications that will be used to focus the intervention.

The primary outcome measure is the difference between intervention and control group in change in cardiovascular risk score. For this purpose blood pressure, HbA_1c_, total and HDL-cholesterol and smoking status will be assessed. Secondary outcome measures are quality of life, patient satisfaction, physical activity, eating behaviour, smoking status, depression and determinants of behaviour change. Differences between changes in the two groups will be analysed according to the intention-to-treat principle, with 95% confidence intervals. The power calculation is based on the risk for cardiovascular disease and we calculated that 97 patients should be included in every group.

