#### Intervention group

Patients who are assigned to the intervention group receive CBT in addition to the same managed care. The CBT is performed by diabetes nurses and dieticians, who received a training of two days in the performing of CBT prior to the onset of the study. Additionally, two instruction days on the implementation of the intervention were arranged. A treatment manual is used during the study to guide the treatment. All CBT sessions are tape-recorded to assess treatment fidelity of the diabetes nurse or dietician to the protocol. In addition, these tape-recordings are used in supervision sessions to provide ongoing feedback. Each diabetes nurse and dietician haves supervision once every four weeks with a psychologist ([name]) who is specialised in CBT. This psychologist is also available by email or telephone between the supervision sessions.

A pilot study was performed before the start of the study to provide three practice sessions for each diabetic nurse and dietician and to assess logistic pathways of the study. There were 10 caregivers involved in the study, which means that 30 patients were included in the pilot study. A supervision meeting was scheduled after the pilot study to discuss logistic pathways and skills to perform the CBT of every caregiver.

The CBT starts with a visit to the diabetes nurse. Results of the baseline measurements can be used to motivate the patient to change. With the help of MI techniques, a problem list is created by the patient focused on lifestyle (smoking behaviour, diet and physical activity). When the most important problem is related to smoking or physical activity, the patient visits the diabetes nurse during the next sessions. When the most important problem is related to diet, the patient is rescheduled to visit the dietician during follow-up sessions. From that moment, the patient remains with the same diabetes nurse or dietician during the entire study.

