### Co-interventions and compliance

Co-interventions are avoided during the intervention by means of the fact that the control group was scheduled to a diabetes nurse that did not receive the training on CBT. In addition, all caregivers in the Diabetes Care System have access to the same central database which includes clinical characteristics of the patients and details on given advice and information. This centralisation avoids co-interventions. However, any co-intervention is reported. Compliance to the CBT is assessed by registration of the number of sessions that patients attend.

Compliance to the intervention is considered adequate when at least three sessions are attended. For the patients in the control group, the number of follow-up visits to the diabetes nurse or dietician is also registered. The number of visits to the GPs or hospital is registered for both the intervention and the control group.

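### The planned multilevel model has no level for the roughly ten individual CBT caregivers; if outcomes correlate within caregiver, the interval for the primary effect is too narrow

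*Protocol article*

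**What the plan says.** The Analyses section names the sources of dependence that the multilevel model handles: it is used "to adjust for the clustering of observations of patients receiving care from the same GP, and for repeated measurements within one patient". The covariates listed there include "number of attended sessions, general practitioner, and type of health care provider (diabetes nurse or dietician"). The only provider term is therefore a two-category type, not the individual person.

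The Intervention group section describes who delivers the treatment: "The CBT is performed by diabetes nurses and dieticians, who received a training of two days". On their number it says: "There were 10 caregivers involved in the study, which means that 30 patients were included in the pilot study". Each caregiver had three pilot practice sessions, and 10 × 3 = 30, so these ten are the people trained to give CBT. The first session is with a diabetes nurse. Depending on the main problem, the patient then continues with a nurse or moves to a dietician, and "From that moment, the patient remains with the same diabetes nurse or dietician during the entire study". The Abstract adds that sessions are given one to one, three to six per patient.

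On the comparison arm, the Co-interventions and compliance section says that "the control group was scheduled to a diabetes nurse that did not receive the training on CBT". It makes no such statement about dieticians.

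The Sample size section uses one correlation only, 0.20 within practices.

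**The concern.** Patients treated by the same CBT caregiver share that person's skill and style, so their outcomes may be correlated. Trained nurses see intervention patients and untrained nurses see controls, so such differences do not cancel between arms. They add directly to the variance of the treatment contrast.

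The GP level does not repair this. Randomisation is in blocks within practice, so each practice contributes to both arms. The CBT is given centrally at the Diabetes Care System, and the article nowhere links caregivers to practices. The provider-type covariate separates nurses from dieticians but treats all nurses as one and all dieticians as one.

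At stake are the stated 5% two-sided alpha, the coverage of the 95% confidence interval for the primary outcome, and, under the planned drop-out, the 90% power.

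**Working it through.** **Inputs from the Sample size section.** d = 0.05, sd = 0.10, r = 0.20, two-sided alpha 0.05, power 90%, drop-out 30%; 68 evaluable and 97 randomised per arm.

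**Input from the Intervention group section.** Ten CBT caregivers.

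**Assumptions.** A caregiver ICC of 0.01 to 0.10 (share of the variance left after practice), equal caseloads, and caregiver clustering in the intervention arm only.

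**1. Reproduce the plan's figure.** n = 2(1.96 + 1.282)² × 0.10² × 0.8 / 0.05² = 67.25, rounded up to 68. 68 / 0.7 = 97.1, stated as 97. Both reproduce.

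**2. Caseload.** 68 / 10 = 6.8 with the full drop-out; 97 / 10 = 9.7 with none.

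**3. Variance.** Design effect in the CBT arm: DE = 1 + (m − 1) × ICC. True variance of the difference over the variance the model reports: V = (DE + 1) / 2. Example with m = 6.8 and ICC = 0.05: DE = 1 + 5.8 × 0.05 = 1.29 and V = 1.145, so the true standard error is √1.145 = 1.07 times the reported one.

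**4. Type I error and power.** Type I error = 2[1 − Φ(1.96 / √V)]. Power with the correct standard error = Φ(0.05 / (SE√V) − 1.96), where SE = √(2 × 0.01 × 0.8 / n), which is 0.0153 at n = 68.

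| Per arm | ICC | DE | True SE / reported SE | Type I error | Power |
|---|---|---|---|---|---|
| 68 | 0 | 1.000 | 1.00 | 5.0% | 90.3% |
| 68 | 0.01 | 1.058 | 1.01 | 5.3% | 89.5% |
| 68 | 0.05 | 1.290 | 1.07 | 6.7% | 86.1% |
| 68 | 0.10 | 1.580 | 1.14 | 8.4% | 81.9% |
| 97 | 0.01 | 1.087 | 1.02 | 5.5% | 96.8% |
| 97 | 0.05 | 1.435 | 1.10 | 7.6% | 94.2% |
| 97 | 0.10 | 1.870 | 1.20 | 10.2% | 90.1% |

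**5. Does adjusting for practice remove it?** A simulation used 13 practices, 1:1 allocation within practice, practice as a fixed effect, and ten caregivers in the intervention arm crossed with practice (20,000 runs per scenario). Ignoring caregivers gave a type I error of 4.9 / 5.4 / 6.6 / 8.2% at ICC 0 / 0.01 / 0.05 / 0.10 with 68 per arm, and 5.2 / 5.5 / 7.6 / 10.4% with 97. This agrees with the formula, so practice adjustment does not remove the inflation.

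**6. Number of caregivers.** If eight rather than ten carried the caseload, the type I error at 68 per arm would be 5.4 / 7.2 / 9.5% for ICC 0.01 / 0.05 / 0.10.

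**The case against.** The strongest objection is that everything turns on an ICC that the documents do not give. The design works to keep it low: shared training and instruction days, a manual, taped sessions, and supervision every four weeks. The risk score also contains items that no caregiver can change, such as sex and ethnicity. At an ICC of 0.01 the inflation is trivial. This stands, and it makes the size conditional. It does not remove the omission, because any positive ICC pushes the error in the same direction.

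A reader might infer that the clustering lies wholly in one arm. The text supports that for nurses only. Dieticians may serve both arms, in which case their usual-care effects partly cancel. Control patients also share nurses; with separate control nurses, correlation there would add to the inflation. The one-arm calculation is a simplification.

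A reader might also infer that the 90% power is lost. That holds only towards the planned drop-out: with all 97 per arm retained, power is still about 90% at an ICC of 0.10.

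Caregiver membership is not perfectly clean either. Diet patients see a nurse before the dietician, and the choice of provider follows the patient's main problem, so some similarity within a caregiver is case mix. The provider-type covariate takes up part of that.

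Finally, an article may leave random-effects detail to the full protocol or analysis plan. Here, however, the article does list its levels, and the omission is in that list.

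**Conclusion.** The point holds in conditional form. The stated model omits a source of dependence that the trial's own delivery creates and that the GP level cannot be relied on to absorb. If the caregiver ICC is above zero, the interval for the primary effect is too narrow: the standard error is understated by a factor of 1.01 to 1.14 with 68 per arm and 1.02 to 1.20 with 97, over assumed ICCs of 0.01 to 0.10. The inflation is slight at 0.01 and material from about 0.05.

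These sizes rest on ten caregivers with equal caseloads, all nested in the CBT arm; unequal caseloads would raise the design effect. The documents do not support saying that the intervals are too narrow as a matter of fact, or that the type I error is known to exceed 5%.

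**What to change.** - Add a random intercept for the individual CBT caregiver, active in the intervention arm only (a partially nested model), beside the practice effect. Use small-sample degrees of freedom. Put it in the primary model, or at least in a pre-specified sensitivity analysis.
- Let the term act on the change, or on post-baseline values, since caregivers cannot affect baseline.
- Assign each patient to the caregiver responsible after the first session. Place intervention patients who attend no session under their scheduled nurse, or treat them as singletons.
- For any dietician who serves both arms, use a caregiver effect that spans both arms.
- Report the caregiver ICC, and state that the sample size made no allowance for caregiver clustering.

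The cost is somewhat wider intervals and a variance component that will be imprecise with about ten caregivers. Caregiver identity must be recorded for each patient: the article describes taped sessions, attendance registration and a central database, but does not say that identity is stored. No extra patients or visits are needed.

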### Interventions

#### Control group

Patients allocated to the control group receive managed diabetes care provided by the DCS.

This managed diabetes care consists of three elements. Firstly, these patients are invited by means of a telephone call from the reception of the DCS to make an appointment for an annual physical examination at the medical assistant. Secondly, the patient visits a diabetes nurse and dietician, for 30 minutes each, in order to receive general information and advice on diabetes problems, dietary intake and physical activity. The results of the physical examination and the recommendations of the diabetes nurses and dietician are sent to the patients' GP, in order to stimulate the GP to follow the guidelines of the Dutch College of General Practitioners [17,18]. Thirdly, the DCS coordinates the care of the patient between the general practices and secondary diabetes care.

Patients in the control group are scheduled for one visit to the diabetes nurse and for one visit to the dietician; follow-up visits are optional.

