After the MI phase, is it time to strengthen commitment to a lifestyle change plan. At this point, the patient is willing and able to change. Signs of this readiness for change are: decreased resistance, decreased discussion about the problem, reaching some kind of resolution, increasing change talks, questions about the change, and envisioning how life might be after a change. At this time, the diabetes nurse or dietician makes, together with the patient, an implementation plan where, when and how the behaviour changes will be performed. The formulation of this plan makes it easier for patients to carry out intended actions. This will be done by PST [28-31].

The CBT consists of three to six visits of 30 minutes to the diabetes nurses or dieticians at the DCS. There is a focus on one problem area in each session. During all sessions, both the MI and the PST skills are used to motivate the patients, set new goals and review the patients' progress. The last CBT session is brought to an end by reviewing and emphasising the entire CBT process, with emphasis on achieved successes of the patient and implementation of CBT in the future, independently of the diabetes nurse or dietician. The GPs provide ongoing feedback during the intervention.

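### If the intention-to-treat comparison is adjusted for sessions attended and provider type, as the Analyses section allows, it no longer estimates the effect of adding CBT to managed care

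*Protocol article*

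**What the plan says.** All references are to the protocol article.

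- **Target.** Analyses states: "On the basis of an intention-to-treat analysis, differences in changes between the intervention and the control group are measured with 95% confidence intervals". This covers primary and secondary outcomes at 12 months. A multilevel model and a per-protocol analysis follow.
- **Adjustment.** A separate paragraph of Analyses begins "We will adjust data for possible confounders: age, gender, weight at start of study, diabetes duration" and continues through education to "depression, smoking, number of attended sessions, general practitioner, and type of health care provider (diabetes nurse or dietician"). It does not say which of the preceding analyses it governs.
- **Sessions attended.** Co-interventions and compliance makes this the adherence measure: "Compliance to the CBT is assessed by registration of the number of sessions that patients attend". The same section records follow-up visits by controls.
- **Planned level by arm.** Intervention group: "The CBT consists of three to six visits of 30 minutes to the diabetes nurses or dieticians at the DCS". Control group: "Patients in the control group are scheduled for one visit to the diabetes nurse and for one visit to the dietician; follow-up visits are optional".
- **Provider type.** In the CBT arm the first visit is to the diabetes nurse, where the patient draws up a problem list. If diet comes first, "the patient is rescheduled to visit the dietician during follow-up sessions"; otherwise the patient stays with the nurse.

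**The concern.** A confounder of a randomised comparison would have to influence allocation. Sessions attended and continuing provider cannot do that, because they come after allocation and partly result from it. Attendance is the dose of the intervention. The CBT patient's provider follows from what is said at the first CBT visit, whereas a control is scheduled to see both kinds of provider. A nurse-or-dietician code therefore means different things in the two arms and has no obvious value for a control.

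With attendance in the model, the arm coefficient compares CBT with control at equal attendance. The stated primary objective is different: whether CBT added to managed care changes the cardiovascular risk profile. Any benefit delivered through sessions is credited to the attendance term. If better-motivated patients both attend more and improve more, the coefficient is distorted further. Even without either mechanism, the correlation between arm and attendance costs precision. An effective intervention could be reported as weaker than it is, or as showing no clear effect.

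**Working it through.** **1. The plan's own size (Sample size section).** Inputs: d = 5 points, SD = 10 points, r = 0.20, two-sided alpha 0.05, power 90%.

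n = 2(1.96 + 1.282)² × 0.10² × (1 - 0.20) / 0.05² = 67.27, rounded up to 68 per group. With 30% drop-out, 68/0.70 = 97.1, given as 97. Both figures reproduce, and this point changes neither.

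**2. What adjustment does.** For least squares with arm and sessions in the model:

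adjusted arm effect = unadjusted effect - c × (mean sessions in CBT arm - mean sessions in controls),

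where c is the pooled within-arm slope of outcome on sessions. The estimate is left alone only if c is zero or the arms attend equally. The plan itself makes attendance unequal.

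**3. Assumptions, not in the documents.**
- CBT arm: 0 to 6 sessions with probabilities 0.08, 0.06, 0.06, 0.25, 0.20, 0.15, 0.20 (mean 3.68, variance 3.16).
- Controls: either coded 0, or 1 to 4 ordinary visits with probabilities 0.1, 0.6, 0.2, 0.1 (mean 2.3, variance 0.61).
- True effect -5 points, with 0, 50 or 100% of it acting through CBT sessions.
- Residual SD 10 × √0.8 = 8.94; 68 per arm.
- Attendance either unrelated to prognosis, or correlated 0.5 with a motivation factor that itself correlates 0.3 with the residual outcome.
- Ordinary least squares, 1500 runs per scenario; practice level and repeated measures not modelled.

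**4. Hand check (full mediation, attendance not prognostic).** The slope in the CBT arm is -5/3.68 = -1.36.
- Controls coded 0: -5 + 1.36 × 3.68 = 0.
- Control visits counted: the pooled slope is -1.36 × 3.16/(3.16 + 0.61) = -1.14 and the gap in means is 3.68 - 2.3 = 1.38. This gives -5 + 1.14 × 1.38 = -3.43.

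The simulation gives -0.03 and -3.43.

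**5. Simulated estimate and power after adjusting for sessions.**

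| Share via sessions | Attendance prognostic? | Control visits counted | Controls coded 0 |
|---|---|---|---|
| 0% | no | -5.04, 82% | -4.94, 44% |
| 0% | yes | -3.79, 59% | -2.36, 13% |
| 50% | no | -4.22, 68% | -2.38, 13% |
| 50% | yes | -3.05, 43% | +0.18, 5% |
| 100% | no | -3.43, 51% | -0.03, 5% |
| 100% | yes | -2.29, 28% | +2.64, 15% |

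Without sessions in the model, the estimate is -4.9 to -5.1 with 88-91% power in every row. For positive estimates, the percentage is simply the rejection rate.

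**6. Precision.** With control visits counted, the arm-sessions correlation is 0.45 and the variance inflation 1/(1 - 0.45²) = 1.25, so the SE rises by about 12% (√1.25 = 1.12). With controls coded 0, the correlation is 0.83, the inflation about 3.2, and the SE rises from about 1.5 to 2.75.

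**7. Provider type.** No magnitude was computed. This part rests on setting the Control group and Intervention group sections side by side.

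**The case against.** The best defence is that the adjustment sentence stands apart. The intention-to-treat comparison and the multilevel model come first with no covariates named, then the per-protocol analysis, then the adjustment. It might be meant only for a further model, and an analysis plan that is not shown may say which model is primary. This stands as a reason to word the point conditionally. It does not remove the point, because the sentence carries no restriction and calls the two variables confounders.

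A reader might go further and infer that sessions are all but aliased with arm, or that the reported effect would change sign. The documents do not support that. Control follow-up visits are registered, and the Discussion plans to compare intervention and control subgroups by number of sessions, so attendance is evidently counted in both arms. On that coding the correlation is moderate and the estimate keeps its sign throughout. There is also a benign case, with no mediation and no prognostic link, in which the estimate is unbiased and only power falls.

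The contrast in providers should not be overdrawn either. CBT patients also receive the same managed care, and Treatment allocation describes the first session in either arm as involving both nurse and dietician.

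Finally, a reader might infer that follow-up smoking or depression would be used as covariates, since only weight is tied to the start of the study and smoking enters the risk score ("algorithm that includes: age at diagnosis, duration of diabetes, sex, ethnicity, smoking status"). Both are measured at baseline and sit in a list made up mostly of patient characteristics, so this is an ambiguity of wording and not evidence of intent.

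**Conclusion.** The adjustment rule is wrong as written. Sessions attended and provider type are consequences of randomisation and do not belong in a model for the intention-to-treat effect. If they are applied there, a true effect of -5 points is estimated at about -2.3 to -5.0 with 28-82% power when control visits are counted, which is the coding the documents favour. If controls are coded 0, the range starts at about -4.9 with 44% power and passes through zero. A material reversal appears only with full mediation and prognostic attendance together, so it is one end of a range and not a prediction.

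These sizes concern sessions only and depend on assumed attendance, mediation and prognosis. The direction of the argument does not. Analyses does not say how control sessions would be counted, so that choice alone could move the result substantially.

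**What to change.** In Analyses, limit the covariates of the primary and secondary intention-to-treat models to baseline variables and practice, and delete number of attended sessions and type of health care provider from that list. Practice may stay, since randomisation was blocked within it.

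Put the two deleted variables in a separately labelled exploratory analysis. That analysis should keep the Discussion's comparison of attention with intervention, which needs control visits as well as CBT sessions, and should state how control visits are counted.

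As a clarification only, write baseline before depression and smoking.

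The cost is about one sentence for the correction and one for the exploratory analysis. No new data are needed, and 68 evaluable and 97 randomised per group stand.
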